| The primary objective of the Randomised Controlled Trial is to determine the effectiveness of a tailored structured community exercise programme in improving functional outcomes in older adults with a high risk of falls. The primary outcome of interest would be the difference in Short Performance Physical Battery (SPPB) scores between the intervention and control groups at 6 months. It is hypothesized that the intervention group will show ≥ 0.6 points improvements in SPPB scores compared to the control group.  Part 2 secondary objectives are to:   1. Evaluate the effect of the exercise programme on balance confidence 2. Evaluate the effect of the exercise programme on fear of falling 3. Evaluate the effect of the exercise programme on participants’ quality of life 4. Evaluate the effect of the exercise programme on falls rates 5. Evaluate the effect of the exercise programme on healthcare cost 6. Evaluate the adoption of the exercise programme 7. Understand the factors contributing to long-term sustainability of SF for further development and implementation 8. Evaluate the programme’s reach and fidelity |
|  |
| **EXPECTED RIKS AND BENEFITS** |
| There is a slight risk of injuries during the exercise classes. However, all necessary precautions will be taken to minimize this risk and all exercises are supervised by trained personnel. Potential benefits include improved strength, and balance. |
| **STUDY POPULATION** |
| List the number and nature of subjects to be enrolled. |
| The RCT will enrol 260 community-dwelling older adults aged 60 years and above who meet the study’s eligibility criteria, of which, a subset of them will be offered to participate in a qualitative interviews/FGDs to determine the implementation outcome of SF and to understand factors contributing to long-term sustainability of SF for further development and implementation. |
| Criteria for Recruitment and Recruitment Process |

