| **Randomised controlled trial; community-dwelling older adults at high risks of falls**   - To determine the effects of SF on functional outcomes   Control (*n* = 130)   - Education and advice on how to reduce your risk of falls   Intervention (*n* = 130)   - 6-months exercise programme - Education and advice on how to reduce your risk of falls   A study comprising of (i) an open-label, parallel randomized controlled trial, and (ii) qualitative interviews or focus group discussions will be performed to assess the aims of the study. Crucial implementation outcomes, including reach, and fidelity, will also be collected.  Based on sample size calculations for the RCT (details can be found in Section 8), the study will involve 260 older adults aged 60 years and above who are at high risk of falls, and a subset will be recruited for the qualitative interviews/discussions.  After enrolment into the study, allocation concealment will be used to randomize participants to the intervention or control group before the baseline visit. Participants will be followed up prospectively for the next 6 months.  Participants will undergo the following activities.  **Intervention Group**:   - Attend 3 evaluation assessments during the study period. - Participate in 6 months of exercises   The exercises are divided into 2 phases:   - The Steady Feet (SF) exercise programme phase. A twice weekly tailored structured group exercise class that will be conducted for 3 months with community instructors and exercise video. - A 3 months maintenance exercise phase. A once weekly structured community group exercise class selected by participants from a recommended list of exercises [list is provided by the study team].   **Control Group**:   - Attend 3 evaluation assessments during the study period.   Primary Variable   - Functional assessment i.e. Short Physical Performance Battery (SPPB)   Secondary Variable(s)   - Balance confidence i.e. ConfBAL scale - Fear of Falling - Quality of life i.e. EQ-5D-5L - History of injurious falls - Single Leg Stance (SLS) - Four Square Step Test (FSST) - Timed Up and Go (TUG) - 30 second chair stand test (30CST) - 6-minute walk test (6MWT) - Healthcare utilisation - Cost of healthcare utilisation - Competency level of community instructors   Socio-demographic variable(s) and other supportive variables   - Age, gender, ethnicity, marital status, education level, residential type - Anthropometric measurement: weight and height - Measure of co-morbidities, i.e. Charlson Comorbidity Index (CCI) - Physical activity levels i.e. Global Physical Activity Questionnaire (GPAQ) - Satisfaction and open-ended feedback of community providers and instructors - Satisfaction and open-ended feedback of participants - Borg Rate of Perceived Exertion (RPE) - Attendance rate of exercise classes - Uptake rate of community-based exercises   **Study procedures and Visit Schedule**  Randomised controlled trial:  For intervention group:  Participants will take part in 6 months of community-based exercises that will commence within 2 weeks from the baseline visit.   \| Visit \| Visit 1  Baseline^1^  Day 1 \| Visit 2  3-month  Day 90 + 30 days^2^ \| Visit 3  6-month  Day 180 + 30 days \| \| --- \| --- \| --- \| --- \| \| Evaluation assessment visit procedures \| - Functional assessments - Questions on:   - Physical Activity levels   - Confidence balance   - Quality of Life   - History of injurious falls \| - Functional assessments - Questions on:   - Physical Activity levels   - Confidence balance   - Quality of Life   - Healthcare utilisation and related costs   - Programme satisfaction \| - Functional assessments - Questions on:   - Physical Activity levels   - Confidence balance   - Quality of Life   - History of injurious falls   - Healthcare utilisation and related costs   - Programme satisfaction \|   For controls:   \| Visit \| Visit 1  Baseline^1^  Day 1 \| Visit 2  3-month  Day 90 + 30 days \| Visit 3  6-month  Day 180 + 30 days \| \| --- \| --- \| --- \| --- \| \| Evaluation assessment visit procedures \| - Functional assessments - Questions on:   - Physical Activity levels   - Confidence balance   - Quality of Life   - History of injurious falls \| - Functional assessments - Questions on:   - Physical Activity levels   - Confidence balance   - Quality of Life   - Healthcare utilisation and related costs \| - Functional assessments - Questions on:   - Physical Activity levels   - Confidence balance   - Quality of Life   - History of injurious falls   - Healthcare utilisation and related costs \|   ^1^Baseline visit will take place within 50 days from the screening, and within 2 weeks prior to the commencement of the intervention group’s exercise classes.  ^2^Visit 2 will be conducted on a separate day after the last scheduled exercise class has been completed.  Participation in the RCT study is voluntary in nature. Participants may withdraw from participation in the study at any time by informing the study team members. However, data that have been collected until the time of participant’s withdrawal will be kept and analysed.  Qualitative interviews or focus group discussions:  Participation in the qualitative interviews/discussions is voluntary in nature, and the purpose of this portion is to better understand the factors contributing to long-term sustainability of Steady Feet for further development and implementation. The interviews or focus group discussions will be audio-recorded, and participants can request to remove what they mentioned during the sessions. The sessions are expected to last no longer than 2 hours. |

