| Data will be collected via 1) hard copy data collection forms and/or 2) extracted electronically from hospital clinical systems, and/or 3) digital audio recorders. Data will be entered into an electronic database, and together with audio recordings will be stored on a password protected laptop accessible only to the PI, Co-Investigators and study team members. |
| **SAMPLE SIZE AND STATISTICAL METHODS** |
| Determination of Sample Size |
| The primary outcome for the study is the difference in SPPB scores between intervention and control group at 6 months.  We estimated a predicted effect size of around 0.4, at 80% power using a two-sided 0.05 level t-test. Accounting for an attrition rate of around 25%, an estimated sample size of 130 participants per group was obtained. Sample size calculations were calculated with G*Power (ver. 3.1.9.4).  An adaptive design may be used after the interim analysis. Sample size re-estimation may be performed to evaluate the power to detect a statistically significant difference in primary outcome between the intervention group and the control group based on an interim analysis. |

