| Statistical and Analytical Plans **Statistical and Analytical Plans**  Data Sets to Be Analyzed  The primary analysis will include all available data from all participants who were randomized into the intervention or control groups. This is the intention to treat data set.  Analysis of Variable(s)  RCT analysis will accord with the “intention-to-treat” principle. A *p* < 0.05 will be considered as statistically significant.  Categorical data will be presented as frequency (percentage), while continuous data will be presented as mean (standard deviation) for parametric distribution and median (interquartile range) for non-parametric distribution. Group or pre/post comparisons of categorical and continuous variables will be performed using chi-square test/ Fisher’s Exact test and/or ANOVA as appropriate.  Categorical variables might be examined using logistics regression models. Demographics and baseline variables will be examined between groups and might be used for adjustment of the regression models. The between group differences in primary and secondary outcomes will be examined using regression and/or ANOVA models.  Cost analysis will examine total healthcare cost from primary care to acute hospital stays during the study period.  If data transformations (e.g., logarithmic) are used to improve distribution characteristics (e.g., normality, variance homogeneity) for parametric procedures, they will be described in reporting of statistical results.  Audio recordings will be transcribed verbatim, translated if needed, and then analysed using content or thematic analysis.  Interim Analysis Plan  An interim analysis might be conducted when approximately 70 participants per group have a known 6^th^ month primary outcome.  Criteria for Early Termination of the Trial  After the interim analysis, sample size and study power might be re-estimated. There are no plans to terminate the trial early. |
|  |
| **DIRECT ACCESS TO SOURCE DATA/DOCUMENTS** |
| The investigator(s)/institution(s) will permit study-related monitoring, audits and/or IRB review and regulatory inspection(s), providing direct access to source data/document. |
|  |
| **QUALITY CONTROL AND QUALITY ASSURANCE** |

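### The intervention arm alone is taught in group classes, but the sample size assumes independent participants and has no reserve, so 80% power needs a class-level ICC near zero

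*Protocol*

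**What the plan says.** **Design.** Under Study Design and Procedures, "allocation concealment will be used to randomize participants to the intervention or control group before the baseline visit", so the individual is the unit of randomisation. The first phase of the intervention is "A twice weekly tailored structured group exercise class that will be conducted for 3 months with community instructors and exercise video". A second three-month phase is a weekly community group class that each participant picks from a list. Controls receive education and advice, and no class is described for them. The competency of community instructors is listed as a secondary variable.

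**Sample size.** Determination of Sample Size reads: "We estimated a predicted effect size of around 0.4, at 80% power using a two-sided 0.05 level t-test". It continues: "Accounting for an attrition rate of around 25%, an estimated sample size of 130 participants per group was obtained". No other inflation appears. Hypothesis and Objectives gives the target on the raw scale: "It is hypothesized that the intervention group will show ≥ 0.6 points improvements in SPPB scores compared to the control group".

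**Analysis.** Statistical and Analytical Plans states: "The between group differences in primary and secondary outcomes will be examined using regression and/or ANOVA models". Baseline variables may be used for adjustment.

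The protocol gives no class size, number of classes or instructors, ICC, design effect, or class or instructor term. The optional interim sample size re-estimation does not mention clustering.

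**The concern.** Participants who share a class and an instructor for three months may have correlated outcomes; controls have no such structure. Positive correlation makes the variance of the intervention mean larger than the independent-observations formula gives, and the control mean is unaffected.

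One of two things follows. If the analysis ignores class, the standard error of the primary comparison is too small and the nominal 5% test rejects too often. If the analysis allows for class, the test is valid but has less than the stated power. The same analysis does not suffer both faults in full.

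The analysis model can still be settled in a statistical analysis plan. The sample size is fixed in the protocol, on an independence assumption that the design does not support.

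**Working it through.** **Inputs from the protocol:** standardised effect d = 0.4, two-sided alpha 0.05, 80% power, 25% attrition, 130 per arm. Completers per arm: 130 × 0.75 = 97.5. The target of 0.6 points with d = 0.4 implies an SD of 0.6/0.4 = 1.5, which is not stated.

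**Assumed, because the protocol does not give them:** m analysed participants per class, and the class-level ICC.

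**1. Reproduce the stated figure.** n = 2(1.960 + 0.842)²/0.4² = 98.1 per arm, and 98.1/0.75 = 130.8, which matches 130. The exact t-test needs 99.1, or 100 per arm, which is 134 after attrition. The figure reproduces only with no design effect.

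**2. Check for reserve.** With 97.5 per arm and ICC 0, SE = √(2/97.5) = 0.143 in SD units. Power = Φ(0.4/0.143 − 1.96) = 79.8%; the t-test gives 79.4%. There is no margin.

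**3. Add clustering in one arm only.** DE = 1 + (m − 1) × ICC and Var(difference) = (DE + 1)/97.5, with equal total variance in the two arms.

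Example, m = 10 and ICC 0.05: DE = 1.45 and SE = √(2.45/97.5) = 0.1585, which is 1.107 times the SE that ignores class. Type I error ignoring class = 2[1 − Φ(1.96/1.107)] = 7.7%. Valid power = Φ(0.4/0.1585 − 1.96) = 71.3%.

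**4. Allow for the small number of classes.** With k = 97.5/m classes, the Satterthwaite df = (v₁ + v₀)²/[v₁²/(k − 1) + v₀²/96.5], where v₁ = DE/97.5 and v₀ = 1/97.5. At m = 10, k = 9.75; with ICC 0.05, df is about 24 and power from the noncentral t is 67.8%.

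| m | ICC | DE | SE ratio | Type I error if class ignored | Valid power, normal | Valid power, Satterthwaite |
|---|---|---|---|---|---|---|
| 6 | 0.01 | 1.05 | 1.012 | 5.3% | 78.8% | 77.2% |
| 10 | 0.01 | 1.09 | 1.022 | 5.5% | 78.0% | 75.3% |
| 10 | 0.02 | 1.18 | 1.044 | 6.0% | 76.3% | 73.3% |
| 10 | 0.05 | 1.45 | 1.107 | 7.7% | 71.3% | 67.8% |
| 15 | 0.05 | 1.70 | 1.162 | 9.2% | 67.1% | 60.7% |

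Part of the last column is the price of having few classes. At m = 10 and ICC 0 the formula gives df = 4/(1/8.75 + 1/96.5) = 32 and power 77.3%.

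An analysis that ignores class keeps a rejection rate of about 79-77% under d = 0.4 at m = 10 and ICC 0.01-0.05, so its fault is the type I error, not lost power.

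**5. Effect of covariate adjustment.** Assume a correlation of 0.5 between an earlier SPPB score and the 6-month score, so that the variance is multiplied by 1 − 0.5² = 0.75. At m = 10, with Satterthwaite degrees of freedom:
- ICC 0.02: 84.7% if adjustment shrinks the class variance in proportion, 83.6% if it leaves that variance unchanged.
- ICC 0.05: 79.8% and 77.2% respectively.

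**The case against.** **The analysis half is silence, not error.** A reader might infer that the planned analysis treats everyone as independent and that its standard errors are too small. The protocol does not say that. Regression can carry a random class effect or cluster-robust errors, and an analysis plan not shown here may specify one. This objection stands. Only the independence assumption in the sample size is on the page.

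**The size rests on assumed inputs.** This also stands. With classes of 6 and ICC 0.01, the type I error is 5.3% and power is about one point below its ICC-zero value by normal approximation. The protocol gives no basis for choosing an ICC, so a flat statement that the trial is underpowered would go too far.

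**The clustering may be weaker by month 6.** Participants move to self-chosen classes for the last three months, so Steady Feet classmates may disperse and the clustering may be diluted or cross-classified. That is fair, and a single class intercept is a simplification. But the second phase is again delivered in groups, so it does not restore independence.

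**Only one arm is clustered.** A full cluster-trial inflation would overstate the problem. The figures above apply the design effect to the intervention arm alone.

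None of this answers the lack of reserve: the stated 130 per arm reaches 80% only if participants are effectively independent.

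**Conclusion.** The point holds in conditional form. The design is partially nested, the sample size makes no allowance for it, and 80% power is not delivered unless the class-level ICC is near zero. Assuming 10 per class and ICC 0.01-0.05, either the type I error is about 5.5-7.7% (class ignored) or valid power is about 78-71% by normal approximation and 75-68% with Satterthwaite degrees of freedom (class modelled).

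A reader might also infer that covariate adjustment makes 260 sufficient whatever the clustering. The figures do not support that: at 10 per class and correlation 0.5, power is about 84-85% at ICC 0.02 but only 77-80% at ICC 0.05. The correlation is itself an assumption, and restricting entry to SPPB 7-10 could weaken it. Nor do the figures show that more participants are needed; that depends on inputs that the protocol should state.

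This should be fixed. Confidence is moderate: firm on the structure and the missing reserve, conditional on the size.

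**What to change.** 1. Record the Steady Feet class and instructor, and the maintenance class, for each intervention participant while the programme runs. If this is not captured then, the valid analysis may be impossible later.
2. Analyse the primary outcome with a partially nested mixed model: a random class intercept in the intervention arm only, arm-specific residual variances, and small-sample degrees of freedom. Use the maintenance class in a sensitivity analysis.
3. Adjust for SPPB, naming which measurement is used. The screening score precedes randomisation; the baseline visit follows it. This recovers much of the lost power.
4. Restate the power of the existing 260 over a stated range of class sizes and ICCs, using the same degrees of freedom. If the interim re-estimation is kept, base it on the same model.

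The cost is a few data fields, a paragraph of analysis text and a revised power statement. The downside is slightly wider confidence intervals and a less favourable stated power.

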| **Schedule of Data Collection (RCT)**   \| Assessments \| Baseline  Day 1 \| 3-month  Day 90 + 30 days \| 6-month  Day 180 + 30 days \| \| --- \| --- \| --- \| --- \| \| Socio-demographic variables \| X \| - \| - \| \| CCI \| X \| - \| - \| \| SPPB \| X \| X \| X \| \| SLS \| X \| X \| X \| \| Four Square Step Test (FSST) \| X \| X \| X \| \| Timed Up and Go (TUG) \| X \| X \| X \| \| 30 second chair stand test (30CST) \| X \| X \| X \| \| 6-minute walk test (6MWT) \| X \| X \| X \| \| Borg Rate of Perceived Exertion (RPE) \| X \| X \| X \| \| Fear of Falling \| X \| X \| X \| \| ConfBAL scale \| X \| X \| X \| \| Global Physical Activity Questionnaire (GPAQ) \| X \| X \| X \| \| EQ-5D-5L \| X \| X \| X \| \| History of injurious falls \| X \| - \| X \| \| Participant satisfaction survey \| - \| X \| X \| \| Provider satisfaction survey \| - \| X \| - \| \| Healthcare utilisation \| - \| X \| X \| \| Cost of healthcare utilisation \| - \| X \| X \| \| Other implementation outcomes   - Enrolment rates - Retention rates - Completion rates - Adherence to programme protocol - Dosage of intervention \| X \| X \| X \|   Note:   - Baseline socio-demographic variables and CCI will be obtained from community screening and clinical records. - Age will be captured as participant’s age at the point of enrollment - Healthcare utilisation and cost would include ED visits, SOC visits, primary care visits, and hospital admission during the entire 6-month study period. Data might be extracted from clinical records. - Implementation outcomes such as enrolment, retention, dosage of intervention and completion rates will be obtained from administrative records that are captured routinely as part of the study. - Information on adherence to the programme protocol will be obtained from the same competency checklist administered to community instructors under the part 1 feasibility study. |
| **SAFETY MEASUREMENTS** |
| Definitions |

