| Serious adverse event (SAE) in relation to human biomedical research, means any untoward medical occurrence as a result of any human biomedical research which:   - results in or contributes to death - is life-threatening - requires in-patient hospitalisation or prolongation of existing hospitalisation - results in or contributes to persistent or significant disability/incapacity or - results in or contributes to a congenital anomaly/birth defect - results in such other events as may be prescribed   Adverse event (AE) in relation to human biomedical research means any untoward medical occurrence as a result of any human biomedical research which is NOT serious. Adverse event can be any unfavourable and unintended sign (including an abnormal laboratory finding), symptom, or disease possibly/ probably/ definitely associated with the participant in the human biomedical research. |
| Collecting, Recording and Reporting of Serious Adverse Events (SAEs) to CIRB |
| Only related SAEs (definitely/ probably/ possibly) will be reported to CIRB. Related means there is a reasonable possibility that the event may have been caused by participation in the research. Please refer to the CIRB website for more information on Reporting Requirement and Timeline for Serious Adverse Events.  The investigator is responsible for informing CIRB after first knowledge that the case qualifies for reporting. Follow-up information will be actively sought and submitted as it becomes available.  Related AEs will not be reported to CIRB. However, the investigator is responsible to keep record of such AEs cases at the Study Site File. |
| Safety Monitoring Plan |
| The study team will conduct, at least, quarterly meeting to review the study data. Study data to be reviewed will include compilation of data obtained from study and any adverse events and/or serious adverse events recorded to ensure that patient safety is adhered. |
| Complaint Handling |
| Any participant complains will be raised to the PI and dealt with on a case-by-case basis. |
| **DATA ANALYSIS** |
| Data Quality Assurance |
| Data will be routinely reviewed for the purposes of tracking the progress of the study, assuring accuracy, and completeness of the data. Adverse events or serious adverse events will be recorded and monitored to ensure the safety of the participants. |
| Data Entry and Storage |

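### Adverse events count only when attributed to the research, so recorded AE and SAE counts are not comparable between the open-label exercise and education-only arms

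*Protocol*

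**What the plan says.** **Definitions (Protocol, Safety Measurements).** Both terms contain causation. An adverse event "means any untoward medical occurrence as a result of any human biomedical research which is NOT serious", and the sentence after it describes such an event as "possibly/ probably/ definitely associated with the participant in the human biomedical research". The serious category opens in the same way: "Serious adverse event (SAE) in relation to human biomedical research, means any untoward medical occurrence as a result of any human biomedical research which", followed by the usual seriousness criteria.

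**Reporting and record keeping (section on SAEs to CIRB).** "Only related SAEs (definitely/ probably/ possibly) will be reported to CIRB". Related AEs do not go to the board, but "the investigator is responsible to keep record of such AEs cases at the Study Site File". The words 'such AEs' point back to the related ones.

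**General statements.** Data Quality Assurance says that AEs and SAEs are recorded and monitored. The Safety Monitoring Plan provides for a review at least quarterly, covering study data as well as recorded AEs and SAEs.

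**Design.** The trial is open-label. One arm has group classes twice weekly for 3 months and once weekly for 3 more, plus education. The other has education and advice. Both attend three assessment visits. The risk named in advance is injury in class: "There is a slight risk of injuries during the exercise classes".

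**Collected in both arms without an attribution condition.** The data collection schedule has injurious falls at baseline and 6 months. It has healthcare use at 3 and 6 months, covering "ED visits, SOC visits, primary care visits, and hospital admission during the entire 6-month study period". It has no row for adverse events.

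**The concern.** Limiting what goes to an ethics board to related serious events is ordinary. Here the same condition sits inside the definitions, so it also decides what counts as a harm and what is written down.

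Attribution is not a neutral filter in this design. The judgement is made with the arm known, and controls have far less study exposure to which an event could be attributed. The same strained knee may be an AE for a participant who attends classes and a non-event for a control.

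The record could then show an excess with exercise that is not real. If staff tend to judge events unrelated, it could instead leave too few to show a real one. Either would cloud the harm side of a programme that the sponsor hopes to sustain and develop further in older people at high risk of falls. Because this is a collection rule, no later analysis plan can recover events that were never recorded.

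**Working it through.** **1. Does any other text widen the recording?** Three places could do so.

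- *Data Quality Assurance* promises to record AEs and SAEs, but uses the two defined terms. An event judged not to result from the research is neither, so the promise does not reach it.
- *The record-keeping sentence* is expressly about related AEs.
- *The schedule* has no AE row, so no visit procedure asks both arms the same all-cause question.

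On the text as written, events judged unrelated fall outside what is kept as an AE or SAE.

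**2. Which harms are still captured in both arms whatever the cause?**

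| Event | Captured without attribution? | Where |
|---|---|---|
| Injurious fall | Yes, asked at baseline and 6 months | Schedule |
| ED, SOC or primary care visit, hospital admission | Yes, over 6 months | Schedule, note |
| Strain, pain or other injury with no injurious fall and no care sought | No | – |
| Fall without injury, no care sought | No | – |
| Death | Not listed | – |

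The third row is a plausible form of the one risk that the protocol names.

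**3. How far could the filter distort recorded counts?** The protocol gives no adverse event rate and no attribution rate, so this is illustration on assumed values. The only input from the plan is 130 participants per arm.

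Let r be the true event risk in an arm and a the probability that an event is attributed to the research.

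- Expected recorded events = 130 × r × a.
- At equal r, the apparent ratio is a(exercise) ÷ a(control), whatever r is.

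With r = 20% in both arms there are 130 × 0.20 = 26 true events per arm:

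| a, exercise | a, control | Recorded, exercise | Recorded, control | Apparent ratio (truth = 1) |
|---|---|---|---|---|
| 50% | 50% | 13.0 | 13.0 | 1 |
| 50% | 10% | 13.0 | 2.6 | 5 |
| 30% | 5% | 7.8 | 1.3 | 6 |

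- **Range of r.** At 50% against 10% attribution, the false risk difference is r × (0.50 − 0.10): 4 points at r = 10%, 8 at 20% and 12 at 30%.
- **A true benefit reversed.** With true risks of 20% (exercise) and 30% (control), the true ratio is 0.67. Recorded events are 130 × 0.20 × 0.50 = 13.0 and 130 × 0.30 × 0.10 = 3.9, an apparent ratio of 3.3.
- **A true excess made too sparse to see.** With true risks of 20% (exercise) and 10% (control), and 5% attribution in both arms, recorded events are 130 × 0.20 × 0.05 = 1.3 and 130 × 0.10 × 0.05 = 0.65.

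The first row shows that the filter does no comparative harm when attribution is equal. The problem is that this design gives no reason to expect equality.

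**The case against.** The strongest reply is that much of the remedy is already in the protocol, and a good deal of it stands.

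- **Falls and care use are collected in both arms.** This is correct. Utilisation is a secondary variable separate from its cost, and the Statistical and Analytical Plans section examines secondary outcomes between groups by intention to treat. A reader might infer that harms cannot be compared at all, but the documents do not support that.
- **The quarterly review is not confined to attributed events.** Also correct: it covers study data as well. The filter applies to the AE and SAE part of what it sees.
- **Controls can have related events.** Correct. Relatedness refers to participation in the research, and controls perform balance, chair-stand and walking tests at three visits. Attribution in controls may be low, but it need not be zero.
- **The wording is ambiguous.** Specifying related SAEs for reporting would be redundant if unrelated ones were never identified, so the authors may have meant to record everything. That may be the intention, but the definitions and the record-keeping sentence do not say it.

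A reader might also build a dramatic figure from the background section. Annual fall proportions of 18.6% to 50%, halved for 6 months, give 130 × 0.093 = 12.1 to 130 × 0.25 = 32.5 fallers per arm. One-third seeking care gives 4.0 to 10.8 medically attended falls. Calling 7 related in one arm and none in the other gives 7/130 against 0/130, Fisher p = 0.014. The arithmetic is right, but it does not measure the problem. It chooses 100% against 0% attribution. It uses events that the utilisation data capture anyway, and it tests a comparison that the protocol does not plan. The 50% refers to people with a previous fall, which is not an eligibility criterion.

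**Conclusion.** The point holds in a limited form. The protocol's definitions and record-keeping rule filter AEs and SAEs by an attribution judgement made with the arm known, so those counts are not comparable between arms. Injurious falls and healthcare use give a partial comparison free of attribution. The real gap is minor and non-fall injury for which no care is sought, falls without injury, and deaths.

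The size cannot be derived from the documents. The ratios of 5 and 6 above rest wholly on assumed attribution rates. A bias against exercise is the more plausible direction, because that arm has the classes to which events can be attributed, but the text does not settle it. The reporting rule to the ethics board is not itself at fault. A missing safety table layout is not part of the point either, since an analysis plan may supply one. What an analysis plan cannot supply is data that the collection rule left out.

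**What to change.** 1. **Keep** the CIRB rule, with related SAEs only.
2. **Remove attribution from the definition used for recording.** For the study's own records, an adverse event is any untoward medical occurrence from baseline to 6 months, in either arm, whatever its cause. Relatedness is graded in a separate field.
3. **Add an AE row to the schedule at the 3- and 6-month visits**, with the same question in both arms. It should cover falls, musculoskeletal injury or pain, ED visits, admissions and deaths. Repeating only the items already collected would leave the gap open.
4. **Mark how each event came to light.** Class participants meet instructors weekly or more often, so events volunteered there should be kept but distinguished from those elicited at the common visits.
5. **Tabulate by arm** with the difference and 95% CI, and relatedness as an extra column. Give the same table, with the injurious-fall and utilisation data, to the quarterly safety review.

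The cost is a short wording change, slightly more recording at visits that already take place, and one extra table. It should be made as early as possible, because events not recorded at the time cannot be reliably recovered.
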